## Abstract

**Background:**

Accidental Accidental awareness during general anesthesia (AAGA) occurs in 1–2% of high-risk practice patients and is a cause of severe psychological trauma, termed post-traumatic stress disorder (PTSD). However, no monitoring techniques can accurately predict or detect AAGA. Since the first reflex for a patient during AAGA is to move, a passive brain-computer interface (BCI) based on the detection of an intention of movement would be conceivable to alert the anesthetist. However, the way in which propofol (i.e., an anesthetic commonly used for the general anesthesia induction) affects motor brain activity within the electroencephalographic (EEG) signal has been poorly investigated and is not clearly understood. For this reason, a detailed study of the motor activity behavior with a step-wise increasing dose of propofol is required and would provide a proof of concept for such an innovative BCI. The main goal of this study is to highlight the occurrence of movement attempt patterns, mainly changes in oscillations called event-related desynchronization (ERD) and event-related synchronization (ERS), in the EEG signal over the motor cortex, in healthy subjects, without and under propofol sedation, during four different motor tasks.

**Methods:**

MOTANA is an interventional, prospective, exploratory, physiological, monocentric, and randomized study conducted in healthy volunteers under light anesthesia, involving EEG measurements before and after target-controlled infusion of propofol at three different effect-site concentrations (0 *μ*g.ml ^−1^, 0.5 *μ*g.ml ^−1^, and 1.0 *μ*g.ml ^−1^). In this exploratory study, 30 healthy volunteers will perform 50 trials for the four motor tasks (real movement, motor imagery, motor imagery with median nerve stimulation, and median nerve stimulation alone) in a randomized sequence. In each conditions and for each trial, we will observe changes in terms of ERD and ERS according to the three propofol concentrations. Pre- and post-injection comparisons of propofol will be performed by paired series tests.

**Discussion:**

MOTANA is an exploratory study aimed at designing an innovative BCI based on EEG-motor brain activity that would detect an attempt to move by a patient under anesthesia. This would be of interest in the prevention of AAGA.

**Trial registration:**

Agence Nationale de Sécurité du Médicament (EUDRACT 2017-004198-1), NCT03362775. Registered on 29 August 2018. https://clinicaltrials.gov/ct2/show/NCT03362775?term=03362775&rank=1

**Electronic supplementary material:**

The online version of this article (10.1186/s13063-019-3596-9) contains supplementary material, which is available to authorized users.

## Background

Every year, several hundred million surgeries are performed worldwide [1]. Among these surgical procedures, 0.1–0.2% of patients are victims of an accidental awareness during general anesthesia (AAGA), i.e., an unexpected awakening of the patient during a surgical procedure under general anesthesia [2–4]. The estimated number of AAGAs can increase up to 1% in high-risk practice patients, despite apparently appropriate anesthesia administration [4–6]. Considering the high occurrence of this phenomenon, new solutions need to be found to solve this issue.

Beyond the terrifying aspect of this experience, AAGA can cause severe psychological trauma, called post-traumatic stress disorder (PTSD) [7]. Seventy percent of AAGA events are complicated with PTSD, resulting in many negative repercussions on the victim’s life: anxiety, increased risk of suicide, insomnia, chronic fear, flashbacks, and lack of confidence in the medical staff [2, 3, 8, 9]. In addition, AAGAs may also generate legal claims that induce an additional cost for the hospital [2, 6].

Unfortunately, there are currently no satisfactory monitoring solutions sufficient to evaluate the depth of general anesthesia and detect intraoperative awakening [10, 11]. The anesthesiologist’s observation of clinical signs is not sufficient to prevent an AAGA during surgery [12]. New indexes using part of the cortical frontal electroencephalographic (EEG) signal (e.g., Bispectral Index, Entropy, Patient State Index) have failed to demonstrate their reliability and superiority [5, 13–15]. Indeed, current brain monitors available for intraoperative analysis of the cortical frontal EEG may not adequately reflect an attempt of movement from the patient under anesthesia, especially if paralytics (neuromuscular blocker agents) are used.

During an AAGA, there is evidence that the patient’s first reflex is to move to warn the surgical team [16]. However, patients may desperately attempt to move, without success [17] and perform a so-called intention to move. A motor imagery (MI) can be detected by recording the EEG signal over the motor cortex such as in the brain-computer interface (BCI) domain [18, 19]. Indeed, the mu (7–13 Hz) and beta (15–30 Hz) sensorimotor rhythms are characterized, before and during a MI, by a gradual decrease of power in mainly the alpha (mu) and beta bands, and after the end of the MI, by an increase of power in the beta band. These modulations are respectively known as event-related desynchronization (ERD) and event-related synchronization (ERS) or post-movement beta rebound [20–22].

If a BCI based on the MI of a patient seems feasible [23], the impact of propofol on the EEG activity, especially over the motor cortex, is still not yet fully understood. In 2016, Blokland et al. studied the effect of propofol on voluntary subjects who performed movements according to sound beeps while an increasing dosage of anesthetic was administered to them [24]. The authors described the impact of propofol on the EEG signal and showed how the BCI domain could contribute to the issue of AAGAs, but they emphasized that this approach is not a realistic situation, since the patient is explicitly asked to perform a movement. To address this issue, we have shown in a previous article that a frequent stimulation of the median nerve is a very promising approach [23]. Indeed, previous studies have shown that a painless stimulation of the median nerve induces an ERD during the stimulation while an ERS appears after the stimulation [25, 26]. Our recent study showed that a MI was more effectively detected using a median nerve stimulation (MNS). This result highlights promising classification results that would allow us to create a reliable device which can be used in the operating room. Therefore, we can imagine a routine system where the median nerve of the patient would be stimulated, and the analysis of ERD and ERS modulations of the motor cortex would be used to know if the patient has an intention to move. However, this study was conducted without propofol, and the previous results obtained need to be confirmed. The study we propose in this clinical protocol will provide the missing answers to these questions and provide insights into the design of such a BCI.

### Objectives

The main objective is to verify that ERD and ERS patterns can be detected in the cortical motor EEG signal under light general anesthesia conditions according to three different concentrations of propofol at the effect site (0 *μ*g.ml ^−1^, 0.5 *μ*g.ml ^−1^, and 1.0 *μ*g.ml ^−1^) during four different motor tasks (i.e., real movement, motor imagery, motor imagery and MNS, and MNS alone) in a randomized sequence. The secondary objective is to describe how the ERD and ERS generated by an MNS would be modulated according to three different concentrations of propofol. In addition, a combination of MNS and an intention to move will be studied to verify the hypotheses discussed in our previous article [23]. Finally, the forward-looking goal is a translational research project that will allow the development of a new monitoring device for the detection of intraoperative awareness.

For each concentration of propofol, the cortical motor EEG signal will be recorded in several sessions corresponding to the four different motor tasks: during a right-hand voluntary real movement (RM), during a right-hand kinesthetic MI, during a right-hand MNS, and during a right-hand kinesthetic MI followed by a right-hand MNS (MI + MNS). The motor tasks will be performed in a random order according to a computer-generated randomization table. Each motor task will be composed of 50 trials. The four motor tasks will be randomized for each subject in order to avoid fatigue, gel drying, or other confounding factors that might have caused possible biases in the results. At the beginning of each run, the subject will remain relaxed for 15 s. Subjects will be asked to keep their eyes closed (Fig. 1). Figure 2 is the flowchart of the experimental scheme. Figure 3 is the schedule of enrollment, interventions, and assessments. The Standard Protocol Items: Recommendations for Interventional Trials (SPIRIT) checklist is provided as Additional file 1.

**Fig. 1 Fig1:**
[figure not shown]
Paradigm scheme. Paradigm scheme illustrating the organization of the different sessions, tasks, and trials of the study. The study contains 3 conditions of propofol’s concentrations (0 *μ*g.ml ^−1^, 0.5 *μ*g.ml ^−1^, and 1.0 *μ*g.ml ^−1^). For each concentration, 4 motor tasks will be studied (real movement, motor imagery (MI), median nerve stimulation (MNS), and MI + MNS). All motor tasks will start with a sound beep and be followed by a resting state. 50 trials per motor task will be performed

**Fig. 2 Fig2:**
[figure not shown]
Flowchart of experimental scheme. The healthy volunteer subject will be lying down and fitted with an EEG helmet with 128 sensors, 32 of which will be placed at the level of the motor cortex. The signals will be recorded using the OpenViBE software. The infusion of propofol will be performed by an infusion pump with a concentration target

**Fig. 3 Fig3:**
[figure not shown]
Schedule of enrollment, interventions, and assessments

Each trial will be conducted with the following steps: (1) a sound beep indicating to the patient that he/she must perform the action, (2) the action (RM or MI), and (3) a resting state period of a few seconds. During the MNS motor task, the delay will be shorter than 1 s because the stimulation will be very short (0.1 ms) and the motor patterns (ERD and ERS) will also be generated in the EEG. The right-hand median nerve will be stimulated in the same way as for measurement with a conduction velocity or for an evoked potential. The stimulation is a painless transcutaneous stimulation using the specific Micromed device Sd Ltm Stim Energy (Micromed, Mâcon, France). The stimulus intensity will range between 3 and 14 mA. The stimulation duration will be 0.1 ms with a frequency of 5 Hz. We will put the two stimulation electrodes on the right-hand wrist according to the standards [25, 28].

After all three sessions have been completed, the subject will have a 30-min rest period. Then, the subject will complete a 10-min post-experimental questionnaire. Then he/she will complete two surveys of street abilities to assess the subject’s ability to leave the hospital safely: the Chung questionnaire (Appendix 3) and the Aldrete questionnaire (Appendix 4). These two evaluation criteria will be validated by the scientific community and are commonly used for outpatient surgery. After completing the study, the subject will be contacted over the phone 24 h after the experiment by the principal investigator to ensure that everything is fine.

### Study population

In this clinical protocol, we have chosen to conduct the experiment on 30 healthy volunteers and not on patients. To ensure the completion of the study, we have designed a flyer that will be distributed on social networks. Participation in the study will also be compensated up to 80 euros. Indeed, in the case of patients, this would disrupt the functioning and organization of planned operations within the hospital. In addition, healthy volunteers will be able to be trained for the task much more easily than would be the case for patients going through surgery. Healthy volunteers will be exposed to the well-known risks of limited general anesthesia with propofol because the dosages used in this clinical protocol are lower than those that induce a loss of consciousness in healthy subjects. The doses have been determined in order to prevent the subjects from being at any risk of loss of consciousness, which will allow them to perform the required motor tasks properly. Finally, the study population will only be male, because anesthesia should be avoided for pregnant women, and the detection of pregnancy would complicate the inclusion of subjects and generate additional costs. Female volunteers are initially excluded from the study due to the extra costs generated by the need for pregnancy tests (blood tests) not budgeted. However, in case of significant results in this preliminary study, female volunteers will be subsequently included to confirm the initial findings and make the results more generalizable. Moreover, this study only concerns right-handed people, as the literature has shown significant differences between left-handed and right-handed people. The healthy volunteers will be remunerated with 80 euros in the form of a purchase voucher.

#### Inclusion criteria

To be included in the study, a person must: 
Have received full details of the research organization and signed our informed consent;Be aged between 18 and 28 years old;Be a man;Have a body mass index between 22 and 28;Be right-handed;Have carried out a clinical investigation adapted before the research is carried out;Be affiliated to a social security regime.

#### Exclusion criteria

The study will exclude a person who: 
Is allergic to any of the ingredients in propofol (in particular, soybean oil and egg);Has a known allergy to propofol;Has a history of an anaphylactic reaction during anesthesia;Is a female, due to the impossibility of checking pregnancy status;Is a pregnant or parturient woman or a breastfeeding mother;Is deprived of liberty by a judicial or administrative decision;Is undergoing psychiatric care, admitted to a health or social institution for purposes other than research, subject to a legal protection measure (guardianship, curatorship, protection of justice), or in an emergency situation;Is an adult who is unable to consent and who is not subject to a legal protection measure;Has a condition that may interfere with EEG recording (i.e., diabetes, polyneuropathy, epilepsy, depression);Is a toxic addict.

### Ethics and trial registration

The study will be conducted in accordance with the principles of the Declaration of Helsinki and the Medical Research Involving Human Subjects Act [29]. This study has been approved by a national ethical committee (Comité de Protection des Personnes Ile de France 1) under number CPPIDF1-2018-ND16. The experiment has also been approved by the Agence Nationale de Sécurité du Médicament (*N*^∘^ EUDRACT 2017-004198-15). Finally, the study protocol was registered on ClinicalTrials.gov (NCT03362775). All patients will give written informed consent before study inclusion and randomization. Patient participation is voluntary; the participant can request to stop participation in the study at any time.

### EEG data acquisition

EEG signals will be acquired using the *OpenViBE* platform [30] with a *Biosemi Active* Two 128-channel EEG system, arranged in the *Biosemi*’s ABC system covering the entire scalp at 2048 Hz. Among all recorded sites, some of the electrodes will be localized around the primary motor cortex, the motor cortex, the somatosensory cortex, and the occipital cortex, which will allow us to observe the physiological changes due to the RM, the kinesthetic MI, and the MNS [25, 26, 31, 32]. An external electromyogram (EMG) electrode will be added in order to verify that there was no movement during the MI task. All offline analyses will be performed using the EEGLAB toolbox [33] and Matlab2016a (The MathWorks Inc., Natick, MA, USA). Considering the large number of electrodes used in this study (128) and the purpose of this research (motor patterns over the motor cortex), we chose to use a common average referencing (CAR) performed using EEGLAB [34, 35]. The results will also be observed by applying a Laplacian filter and a mastoidal re-referencing [36]. Then, the EEG signals will be resampled at 128 Hz and windowed into 9-s epochs corresponding to 1 s before and 5 s after the motor task for each run.

We will compute the ERD/ERS% using the “band power method” [37]: 
1$$ ERD/ERS\%=\frac{\overline{x^{2}}-\overline{BL^{2}}}{\overline{BL^{2}}}\times{100} \enspace,  $$

where $\overline {x^{2}}$ is the average of the squared signal smoothed using a 250-ms sliding window with a 100-ms shifting step, $\overline {BL^{2}}$ is the mean of a baseline segment taken at the beginning of the corresponding trial, and ERD/ERS% is the percentage of the oscillatory power estimated for each step of the sliding window. A positive ERD/ERS% indicates a synchronization, whereas a negative ERD/ERS% indicates a desynchronization. This percentage was computed separately for all EEG channels. The EEG signal was filtered in the mu rhythm (7–13 Hz), in the beta band (15–30 Hz), and in the mu+beta band (8–30 Hz) for all subjects using a 4 ^*t*^*h*-order Butterworth band-pass filter.

ERD and ERS are difficult to observe from the raw EEG signal; an EEG signal expresses the combination of activities from many neuronal sources. We will use the averaging technique to represent the modulation of power of the mu and beta rhythms during the MI, MNS + MI, and MNS conditions since it is considered one of the most effective and accurate techniques used to extract events [20, 38].

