### Statistics

For each trial (*n* = 50), ERD and ERS modulations will be computed in the 8–30 Hz frequency band for the [–2;6]s time window. This time window was chosen according to the ERD occurrence during the motor task (i.e., 2 s for RM, MI, and MI+MNS) and the time required for the ERS to return to the baseline [21]. For each trial, an ERD max and an ERS max will be selected in both their respective time windows ([0;2]s and [4;6]s). For the MNS task, in accordance with the literature [26, 27], the ERD ERS max will be respectively selected in [0.25;0.5]s and [2;4]s after stimulation. An average over the 50 ERDs max and 50 ERSs max will be performed for the motor tasks (MR, MI, MNS, MI+MNS) and each concentration (0 *μ*g.ml ^−1^, 0.5 *μ*g.ml ^−1^, and 1 *μ*g.ml ^−1^). These two values will be compared with each other for each motor task during the three concentrations with a Student’s *t* test (*p* value <0.05).

The ERD and ERS will also be visualized as event-related spectral perturbations (ERSPs). ERSPs allow one to visualize event-related changes in the average power spectrum relative to a baseline of 1.5 s taken 2 s before the auditory cue for all motor tasks and different propofol concentrations [39]. A surrogate permutation test (*p* <0.05; 2000 permutations) from the EEGLAB toolbox will be used to validate differences in terms of time-frequency of this ERSPs. In addition to this analysis, we will apply a false discovery rate (FDR) correction test in order to clarify how the FDR will be controlled for multiple comparisons. This test consists of repetitively shuffling values between conditions and recomputing the measure of interest using the shuffled data. It will be performed by drawing data samples without replacement and is considered suitable to show the difference for all motor tasks during different concentrations of propofol [40].

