### Data collection

Data will be collected with the use of the case report form (CRF), which will be prospectively maintained from the time the patient signs the informed consent until the completion of the study. Patient data will be anonymized; each individual will be given a unique study number (first letter of the first name and first letter of the last name, supplemented by a number assigned to the inclusion, in accordance with Reference Methodology MR001). The data monitoring committee is the Direction de la Recherche et de l’Innovation (sponsor) of the University Hospital of Nancy. An independent data monitoring committee is also nominated to assess serious adverse reactions.

The CRF will contain: 
Demographic data for each patient;Adverse events that may occur during the study;The monitoring data (blood pressure, heart rate, saturation);EEG data, which will be recorded electronically and stored on a computer remaining in the hospital under the supervision of the investigating anesthetist.

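### In the real-movement task, ERD/ERS is averaged over all 50 trials with no check that the sedated volunteer moved, so a drug effect on the signal is mixed with missed or late responses that EMG could identify

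*Protocol article*

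**What the plan says.** All references are to the protocol article.

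- **Trial count.** Study design: "Each motor task will be composed of 50 trials". This applies at each of three concentrations, which rise in the order 0, 0.5 and 1 µg/ml.
- **Averaging rule.** Statistics: "An average over the 50 ERDs max and 50 ERSs max will be performed for the motor tasks", at each concentration. For RM, MI and MI+MNS, the per-trial ERD max is taken in [0;2] s and the ERS max in [4;6] s.
- **Comparison.** Statistics: "These two values will be compared with each other for each motor task during the three concentrations", using a Student's t test at 0.05. The abstract describes the pre/post comparisons as paired.
- **EMG.** EEG data acquisition: "An external electromyogram (EMG) electrode will be added in order to verify that there was no movement during the MI task". The article gives no consequence for an MI trial that does show movement, and no use of EMG in RM.
- **Performance.** Study population says the doses were chosen so that volunteers can carry out the tasks properly. Study design stops the infusion on loss of consciousness. Neither is a check on single trials.
- **Other data.** Data collection lists "The monitoring data (blood pressure, heart rate, saturation") as the monitoring data. The questionnaires come after all three sessions and a 30-minute rest.

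**The concern.** The study asks whether movement-related patterns survive propofol when a person tries to move, so the quantity of interest is the signal given an attempt. In RM the volunteer lies with eyes closed and must act on a beep. A drowsy volunteer may miss some beeps or respond late. A missed trial contributes a value with no movement behind it. A late response can fall partly outside the fixed windows. Either can pull the mean down even if each actual movement produces an unchanged ERD and ERS.

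Non-response is likely to increase with concentration, the variable under test. A fall in the RM mean could then be read as propofol suppressing the motor signal when part or all of it is cue non-response. For a study meant to inform a movement-detection device, these are different conclusions.

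**Working it through.** **No stated figure to reproduce.** The article gives no effect size, SD or power. The inputs it does give are 30 volunteers (abstract: "30 healthy volunteers will perform 50 trials for the four motor tasks"), 50 trials per task and concentration, and alpha 0.05. I take the test as paired and two-sided.

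**Step 1: form of the bias.** Let m be the share of missed trials, A the mean per-trial value when the task is performed (unchanged by propofol) and B the mean value when it is missed.

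- Observed mean = (1 − m)·A + m·B
- False shift = observed mean − A = m·(B − A)

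The shift is zero only if m = 0 or B = A.

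**Step 2: what a missed trial scores.** The endpoint is the most extreme value in a window, so B is not 0. To illustrate, I simulated white noise at 128 Hz and applied a fourth-order Butterworth filter at 8–30 Hz. Power was averaged in 250-ms windows at steps of about 100 ms. The baseline was 1.5 s, starting 2 s before the cue, and the minimum was taken over [0;2] s.

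- Missed trial (no response): B ≈ −54.2%
- Performed trial (assumed true 40% power drop throughout the window): A = 0.6 × (100 − 54.2) − 100 ≈ −72.5%
- Gap: B − A ≈ 18.3 points

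The same holds for ERS. With no response at all, the simulated ERS max over [4;6] s averaged about +84%.

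**Step 3: false shift in mean ERD.**

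| Missed share (assumed) | Shift | Trials left of 50 |
|---|---|---|
| 10% | 0.10 × 18.3 ≈ 1.8 points | 45 |
| 20% | 0.20 × 18.3 ≈ 3.7 points | 40 |
| 30% | 0.30 × 18.3 ≈ 5.5 points | 35 |

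**Step 4: chance of p < 0.05 from the shift alone.** Paired t test, n = 30, df = 29, non-centrality = shift/SD × √30. The SD of paired differences is assumed.

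| Shift | SD 10 | SD 15 | SD 20 |
|---|---|---|---|
| 3.7 points (20% missed) | 50% | 26% | 17% |
| 5.5 points (30% missed) | 83% | 49% | 31% |

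Without missed trials each entry would be 5%.

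**Step 5: after the fix.** If only performed trials are averaged, the mean is A for any m and the false shift is 0. This assumes that non-performance is identified correctly and that misses are unrelated to the size of the response.

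**The case against.** **The article is condensed.** Trial rejection and EMG scoring are routine processing steps that may sit in the full protocol or analysis plan, and 50 may simply be the design count. This has weight: a reader might infer that no check on performance exists anywhere, and the article cannot establish that. But it does state an averaging rule and a single purpose for EMG, and followed as written these leave the RM comparison open to the bias.

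**Performance is protected by design.** Doses below those that cause loss of consciousness, healthy volunteers who can be trained, and a stopping rule all make gross failure unlikely. They do not show that individual beeps were answered.

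**Not every task is affected alike.** A reader might infer that no reduction under propofol can be interpreted. That goes too far. In MNS alone the stimulus itself evokes the ERD and ERS, so there is no action to miss, and this task gives a within-subject reference for a drug effect on the signal.

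**EMG does not solve the imagery tasks.** A reader might infer that the recorded EMG settles the question throughout. It does not. Silence in MI or MI+MNS fits both correct imagery and a missed cue, so EMG confirms performance in RM only.

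**The study is exploratory.** This lowers the cost of a false positive but does not remove the ambiguity in its main outcome.

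**Conclusion.** The point stands for RM: as written, the comparison between concentrations cannot distinguish weaker motor signals from missed or late responses. MI and MI+MNS share the weakness, but EMG cannot resolve it there. MNS alone is free of it.

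The size cannot be derived from the document. The 3.7-point shift, significant in about 50%, 26% or 17% of studies at SD 10, 15 or 20, rests on an assumed 20% missed share, an assumed 40% power drop, assumed SDs and white noise in place of real EEG.

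A larger figure is tempting. If a missed trial scored 0 against a performed −40%, 20% missed trials would move the mean to −32%. That 8-point shift would be significant in about 99%, 81% or 56% of studies at the same SDs. The plan's endpoint does not support this, because selecting an extreme in each trial gives a clearly negative ERD max even with no response.

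**What to change.** 1. Score EMG in every RM trial. Count a trial as performed if a burst follows the beep within the 2-s action window.
2. Compute RM ERD and ERS on performed trials, and keep the average over all 50 as a sensitivity analysis. Performed trials may be the more alert ones, so both results are needed.
3. Report the RM performed-trial rate and EMG latency at each concentration.
4. Remove MI and MI+MNS trials with voluntary EMG activity, not counting any response evoked by the stimulus, and report how many were removed.
5. State as a limitation that missed imagery is invisible on EMG. Read MI and MI+MNS results beside the RM performance rate and MNS alone.

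The cost is some analysis work and fewer RM trials at the higher concentration. It needs no new procedure, provided that the EMG electrode stays in place during RM and picks up the right-hand movement. The article does not say so, and this should be confirmed.

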***Getting closer to the anesthetized state***

Since the first reflex for a patient during an AAGA is to move, a passive BCI based on the intention of movement is conceivable. Indeed, Blokland et al. have shown the feasibility of such a device [24]. However, the challenge of using such a BCI is that the intention to move from the waking patient is not initiated by a trigger that could be used to guide a classifier. In a previous study, we proposed a new solution based on MNS, which causes specific modulations in the motor cortex and can be altered by an intention of movement. We showed that MNS may provide a foundation for an innovative BCI that would allow the detection of an AAGA [23]. More particularly, we verified that MNS modulates the motor cortex by first generating an ERD during stimulation and then an ERS post-stimulation in voluntary subjects. In addition, we have discovered a new post-stimulation rebound ERS (PSR) which appears 250 ms after the stimulation in the mu and low beta bands. MNS combined with the intention to move, i.e., the MI, had a significant impact on the ERD and ERS generated by the MNS. Indeed, despite the fact that the ERD was unaltered, the PSR was almost abolished and the rebound in the beta band was diminished. Those differences have allowed a classification with highly accurate results. With these findings, we showed that a BCI based on MNS is more effective than a BCI based on a MI state versus rest [23]. Our results will be confirmed during the MOTANA clinical protocol, where the same conditions will be used on voluntary subjects sedated with propofol.

If we can find similar results in propofol-sedated subjects, we will plan to repeat the experimentation on subjects under general anesthesia with neuromusclar blockade in order to study RM intention instead of motor imagination. In a final experiment, we could combine both conditions with paralyzed and anesthetized patients in order to investigate if the combination could change the results.

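### The ERD/ERS formula and the ERSP maps do not separate stimulus-locked evoked power from induced mu/beta power, which leaves the early response in the MNS tasks ambiguous

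*Protocol article*

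**What the plan says.** EEG data acquisition computes ERD/ERS% by a band-power formula, Equation 1. The numerator term "is the average of the squared signal smoothed using a 250-ms sliding window with a 100-ms shifting step", and the reference "is the mean of a baseline segment taken at the beginning of the corresponding trial". On averaging, the section says: "We will use the averaging technique to represent the modulation of power of the mu and beta rhythms". It describes no subtraction of the mean waveform and no split into induced and evoked power.

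Study design says the right median nerve "will be stimulated in the same way as for measurement with a conduction velocity or for an evoked potential", with a 0.1-ms stimulus at 5 Hz. The number of pulses per trial is not given.

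Statistics states that "ERD and ERS modulations will be computed in the 8–30 Hz frequency band for the [–2;6]s time window". For MNS alone, the ERD and ERS maxima are "respectively selected in [0.25;0.5]s and [2;4]s after stimulation". For the other tasks, MI+MNS included, the windows are 0–2 s and 4–6 s. The same section compares ERSP maps, which are relative to a baseline before the auditory cue, between conditions by permutation test with FDR correction.

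Objectives makes the propofol effect on ERD and ERS generated by MNS the secondary objective.

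**The concern.** Squaring a filtered single trial keeps everything in the band. That includes the ongoing rhythm, whose power ERD and ERS are meant to describe, and any waveform that recurs at a fixed delay after the stimulus. The protocol calls the result oscillatory power, but here the stimulus is of a kind that produces such a waveform.

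Evoked power is a positive term. It makes an early ERD look shallower and can add power to the early part of a time-frequency map. If its size differs between concentrations, total power differs even when the rhythm does not, and nothing planned would tell the two apart. That distinction is what the secondary objective needs. The early period also matters to the device concept: the Discussion describes a post-stimulation rebound "which appears 250 ms after the stimulation in the mu and low beta bands".

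**Working it through.** **No figure to reproduce.** The protocol gives no evoked amplitude and no size for this effect. The check is algebra plus a simulation on assumed amplitudes.

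**Algebra.** Write the filtered trial as x = s + e, with s the induced rhythm and e the evoked waveform, fixed across trials and independent of s. Then E[x²] = E[s²] + e². Divide by baseline power B, taken to lie before the pulse so that it holds no evoked part:

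observed ERD% = induced ERD% + 100r, with r = e²/B.

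If the evoked amplitude halves, r falls to r/4 and the observed value moves by 75r points with no change in rhythm. The ERSP map at a given time and frequency is also total power relative to a pre-cue baseline, so the same holds there.

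**Size at one fixed time, 0.25 s after the pulse.** Assume late evoked components of 2–4 µV, an 8–30 Hz filter and a baseline power of 10–36 µV².

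- Single pulse, centred 250-ms steps: about 0.5 µV², so 100r = 0.5/36 to 0.5/10, or 1.4 to 5 points.
- Single pulse, trailing steps: about 1.8 µV², or 5 to 18 points.
- 5-Hz train: about 2.2 µV² sustained, or 6 to 22 points.

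With a true ERD of -40%, r = 0.05 gives -35% and r = 0.22 gives -18%. Halving the evoked amplitude moves these to -38.75% and -34.5%.

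**Size in the extracted endpoint.** ERD max is the most negative step in a window, so it can avoid a brief evoked burst. A simulation tested this with 30 volunteers, 50 trials, 128 Hz, an 8–30 Hz Butterworth filter, centred 250-ms windows, 100-ms steps and the windows in Statistics. The induced rhythm was fixed at -40% during ERD and +50% during ERS. The evoked peak before filtering was 0 to 4 times the in-band background SD. The response was short (about 0.15 s) or long (about 0.4 s), after one pulse or five pulses at 5 Hz, with time counted from the first pulse. In MI+MNS the pulse was placed at 750 ms, a figure from the Discussion that may describe the earlier study. The filter was zero-phase unless marked.

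ERD max (%) from Equation 1, rhythm unchanged:

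| Case | 0 SD | 1 SD | 2 SD | 4 SD |
|---|---|---|---|---|
| MNS, one pulse, short | -45.9 | -45.4 | -45.8 | -46.2 |
| MNS, one pulse, long | -45.7 | -46.0 | -46.2 | -43.6 |
| MNS, one pulse, long, causal filter | -46.3 | not run | -44.2 | -37.2 |
| MNS, train, short | -46.5 | -43.2 | -32.1 | +5.4 |
| MNS, train, long | -46.2 | -38.8 | -15.5 | +80.5 |
| MI+MNS, one pulse, short | -72.4 | -72.5 | -72.3 | -71.5 |
| MI+MNS, one pulse, long | -72.7 | -72.3 | -71.8 | -71.3 |
| MI+MNS, train, short | -73.0 | -71.5 | -69.2 | -66.5 |
| MI+MNS, train, long | -72.9 | -71.0 | -67.8 | -64.7 |

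A short response with a causal filter stayed flat. The train matters because its harmonics at 10, 15, 20, 25 and 30 Hz fall in the 8–30 Hz band. ERS max in the 2–4 s and 4–6 s windows ran from 161.9 to 169.0% with no trend across evoked sizes.

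**With the across-trial mean subtracted before squaring.** MNS ERD max stayed between -44.5 and -47.5%, and MI+MNS between -72.2 and -73.0%, for every evoked size, single pulse or train. The causal-filter case was not rerun with subtraction.

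**The case against.** The strongest reply is that the extraction rules already protect most endpoints. The ERS maxima are read seconds after the pulse. The MI+MNS ERD max is taken over 2 s and moves by about 1 point for a single pulse. The MNS window opens 250 ms after stimulation and follows cited literature. With one pulse and a zero-phase filter the MNS ERD max hardly moves. All of this stands.

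The large figures need a train, and Study design calls the stimulation very short. If the MNS window counts from the last pulse, the train figures do not apply. This also stands, and it makes the bias conditional. It does not remove it, because the article gives 5 Hz without a pulse count.

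A reader might infer more: that propofol's effect on the evoked potential will be misread as a change in motor rhythm throughout the MNS tasks, or that it will pass for a lost rebound and hence for an intention to move. The documents do not support this. They say nothing on how 0.5 or 1.0 µg/ml propofol changes the evoked response. The rebound at 250 ms is a finding of an earlier study and not an extracted endpoint here; it could show only in the ERSP maps. Its near-disappearance was seen when MI was added to MNS without propofol, which is a different contrast. Nor was any bias shown for RM or MI, which have no electrical stimulus; the effect of the beep was not quantified.

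A condensed article may leave processing detail to the full protocol. But it does state the power formula, and that formula keeps the evoked term.

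**Conclusion.** The point holds in limited form, as a cheap improvement. Equation 1 and the ERSP power mix evoked and induced power, in a design whose stimulus is expected to produce an evoked response. Two results are exposed: the early post-stimulus part of the ERSP maps in MNS and MI+MNS, where no choice of the most negative step offers protection, and the MNS-alone ERD max.

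For a single pulse the bias in that maximum is small (about 2 points or less), unless the evoked response is both long and large and the filter is causal (about 9 points: -46.3 to -37.2%). For a 5-Hz train reaching into the window, it is about 14 points (short response) or 31 points (long) at 2 SD. The MI+MNS ERD max shifts by at most about 8 points, and only with a train. The ERS maxima in the Statistics windows are not affected; this says nothing about an ERS read in some other, earlier window.

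All sizes rest on assumed evoked amplitudes, waveforms and baseline power, and a false propofol effect further requires that propofol changes the evoked response.

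**What to change.** For the MNS and MI+MNS tasks, compute ERD% and ERSP a second time. Before squaring, subtract from each trial the across-trial mean waveform of the same volunteer, channel, task and concentration, and scale the resulting power by 50/49 for the 50 trials. Report this induced measure beside the Equation 1 total power. Attribute a propofol effect to the motor rhythm only if it is present in the induced measure. State the number of pulses per trial, whether the MNS windows count from the first or last pulse, and whether the filter is zero-phase.

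The cost is a few lines of analysis code and no new data. The limitation is that trial-to-trial jitter in evoked latency leaves a small residue.
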